### Sample Size Considerations

Assuming 7.5% of patients with T2DM and MA meet enhanced targets for BP (<130/80 mm Hg) and TC (<3.5 mmol/L) in the standard care group with an intraclass correlation of .05, an average of 118 patients with MA per practice (ranging from 27 to 549), data are required from 18 practices (9 in each arm) to detect an increase to 18% or higher in the proportion meeting both enhanced targets in the intervention group, with 80% power at the 5% significance level. The inflation for unequal cluster size is based on a coefficient of variation of 1.11 [21]*.*

### Data Extraction

Primary outcome is measured at baseline, 12, and 24 months post randomization in control practices and every 3 months in intervention practices to allow reporting of audit and feedback data to this group of practices.

One line per patient anonymized data is extracted using a standardized morbidity information query and export syntax (MIQUEST) query [22] in line with local governance regulations [23,24]. Time frames for data extraction are shown in Table 1. Data extraction is carried out remotely using Away from My Desk (Away From My Desk Limited, United Kingdom) [25] software. Results are uploaded to a secure online database and transferred to the research team via encrypted National Health Service email systems.

### Analysis Plan

We are using a cluster randomized design with repeated measurements, and therefore, there is a high likelihood that biomedical characteristics may correlate within a cluster. We will perform linear and logistic multilevel regression analyses to study the effects of the intervention with cluster as the random effect, adjusted for the baseline value of the outcome both at practice and individual levels, using the missing indicator method for “missing” baseline data. Data will be analyzed as intention-to-treat, and differences in outcomes measures between the intervention and control groups will be calculated with 95% CI. It is also likely that not all individuals from the control group will have had regular appointments with their GP; hence, we will perform a sensitivity analysis to compare “attenders” at similar time points in the intervention versus control group.

For presentation of baseline data, we will use Pearson chi-square to analyze differences in proportions between intervention and control groups. Independent samples *t* tests will be used to analyze differences in continuous variables between study groups. Statistical analyses of the baseline data and all future analysis will be carried out using STATA version 14 [26].

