### Setting

Eligible practices (using EMIS Web or SystmOne IT systems and a list size of >6000 patients) within the recruitment area of Leicester City and Leicestershire County were sent an invitation summarizing the study design and protocol. Staff members who expressed an interest were offered a meeting with a member of the study team to clarify any queries regarding the study. Informed consent and information governance approval was sought among eligible practices willing to participate and documented from a senior GP partner or practice manager and Caldecott Guardian. Practices were then randomized by a member of the Leicester Clinical Trial Unit (not involved with the study) to the intervention or control arm. A 1:1 randomization was stratified based on size of diabetes register (small practices <600 patients, large practices >600 patients).

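### The outcome model as described omits the register-size stratum used at randomisation; if register size predicts outcome beyond baseline, the reported interval is wider than the design warrants

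*Protocol article*

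**What the plan says.** On allocation, the Setting section states: "A 1:1 randomization was stratified based on size of diabetes register (small practices <600 patients, large practices >600 patients". Register size is the only stratification factor mentioned.

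On analysis, the Analysis Plan states: "We will perform linear and logistic multilevel regression analyses to study the effects of the intervention". The terms that it then gives for these models are the following: "with cluster as the random effect, adjusted for the baseline value of the outcome both at practice and individual levels". It adds a missing-indicator method for absent baseline values, analysis by intention to treat, and that "differences in outcomes measures between the intervention and control groups will be calculated with 95% CI". Register size does not appear in that section. The article does not say how strongly register size relates to meeting the targets, how many practices fell in each stratum, or which reference distribution the intervals will use.

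**The concern.** Stratified randomisation balances the stratification factor between arms, so variation between small- and large-register practices contributes little to the true variability of the treatment estimate. A model that leaves the factor out still counts that variation as residual between-practice variance. The estimate is not biased by this, but its reported standard error is too large when the factor is prognostic.

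The issue deserves attention here because inference rests on 22 practices (12 control, 10 intervention, per Results), where avoidable between-practice variance matters most. The Analysis Plan does more than stay silent on covariates: it names the random effect, the adjustment terms at two levels and the missing-baseline method. A reader would take this as the adjustment set, and the one design factor is not in it.

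**Working it through.** The article gives no figure for the effect of the stratum, so there is none to reproduce. The check asks how much the reported precision would change under stated assumptions.

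**Inputs from the article**
- ICC: "with an intraclass correlation of .05" (Sample Size Considerations).
- Eligible patients and practices: 2721 in 22 practices (Results), so m = 2721/22 = 123.7 per practice. The planning value was similar: "an average of 118 patients with MA per practice (ranging from 27 to 549".
- Practice split: 12 control, 10 intervention (Results).

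**Assumed input**
- R², the share of residual between-practice variance explained by the stratum after baseline adjustment. The documents give no value, so a range is shown.

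**Step 1: analytic ratio of standard errors**

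On the proportion scale, the variance of a practice mean is proportional to ICC + (1 − ICC)/m. With the stratum in the model, the between-practice part shrinks to ICC(1 − R²).

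- Without stratum: 0.05 + 0.95/123.7 = 0.05768.
- R² = 0.10: 0.045 + 0.00768 = 0.05268. Ratio √(0.05268/0.05768) = 0.956, so the standard error without the stratum is 1/0.956 − 1 = 4.6% too large.
- R² = 0.20: 0.040 + 0.00768 = 0.04768. Ratio 0.909, so 10.0% too large.
- R² = 0: ratio 1, nothing lost.

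This uses the unadjusted planning ICC. If baseline adjustment lowers the residual ICC, within-practice variance takes a larger share and the penalty at a given R² is smaller.

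**Step 2: cost of the extra term**

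A practice-level analysis with intercept, arm and practice-level baseline leaves 22 − 3 = 19 degrees of freedom; adding the stratum leaves 18. The ratio of the t multipliers (18 to 19 df) is 1.004, so the cost is about 0.4% in width.

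**Step 3: simulation with baseline already in the model**

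The Step 1 formula does not show how much of a register-size effect the practice-level baseline would absorb. A simulation (3000 runs per scenario, no treatment effect) therefore used 22 practices in two strata of 11, each split 6 control to 5 intervention. Average log-odds were −2.4 (about 8%, near the planning rate: "Assuming 7.5% of patients with T2DM and MA meet enhanced targets"). The ICC was 0.05, and practice effects at baseline and follow-up had correlation 0.6. Analysis was by practice-level regression on the logit scale with baseline adjustment and t-based intervals, as a stand-in for the multilevel model.

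| Stratum gap in log-odds (baseline, follow-up) | Interval width without vs with stratum | Type I error without / with |
|---|---|---|
| 0, 0 | −0.5% | 4.7% / 4.5% |
| 0.3, 0.3 | +1.0% | 4.6% / 5.1% |
| 0.5, 0.5 | +3.5% | 4.7% / 5.2% |
| 0.8, 0.8 | +7.2% | 3.8% / 4.8% |
| 0, 0.3 | +3.4% | 4.0% / 4.9% |
| 0, 0.5 | +9.9% | 3.7% / 5.5% |
| 0, 0.8 | +24% | 1.5% / 4.6% |

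The true spread of the estimate was almost the same with and without the stratum (for example 0.249 in both at 0.5, 0.5). What changes is mainly the reported standard error, and through it the interval and power. The last three rows need register size to affect follow-up but not baseline; the documents give no evidence for that.

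**The case against.** The strongest objection is scope. This is a journal article, the full analysis plan is not shown, and the model sentence neither says that its list is complete nor excludes design factors. A fuller plan may already include the stratum. That limits the point but does not remove it: the article lists its adjustment terms in some detail, and that list does not match the allocation method.

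The second objection is that harm is conditional, and this stands in full. The practice-level baseline will already absorb much of any stable register-size effect, and the documents neither show nor rule out an effect beyond it.

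Three stronger readings are tempting and are not supported:

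- **That precision is certainly being lost.** This needs a residual association that the article does not report. Without one, adding the stratum makes the interval slightly wider.
- **That the planned test is conservative, with a true level below 5%.** This depends on the reference distribution, which the article does not state. Taking 2 × P(t₂₀ > c/√(1 − R²)), c = 2.086 gives 4.0% at R² = 0.10 and 3.0% at R² = 0.20. With a normal multiplier, c = 1.96, the same expression gives 6.4% at R² = 0, 5.2% at 0.10 and 4.0% at 0.20. Omission lowers the rate relative to inclusion, but whether it falls below 5% cannot be read from the document.
- **That 12 versus 10 practices implies confounding by size.** A 6:5 split in each of two equal strata gives 12:10 with identical stratum proportions. Eligible patients per practice do differ (1299/12 = 108 control, 1422/10 = 142 intervention), but that is not register size and does not show how the strata divided.

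**Conclusion.** The point holds in conditional form. Allocation was stratified by register size, and the outcome model as described leaves the stratum out. If register size predicts the 24-month outcome beyond the baseline adjustment, the reported standard error is larger than the stratified design warrants, the interval is wider and power is lower.

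The size is unknown. The analytic figures of about 5% and 10% rest on an assumed 10% or 20% of residual between-practice variance explained and on the planning ICC. The range of about 1% to 7% rests on an assumed log-odds gap of 0.3 to 0.8 acting equally at baseline and follow-up. With no residual association there is no loss. Confidence is high that the described model omits the stratum and that any effect is in this direction; it is low on how large the effect is. The change is worth making because its cost is negligible, not because a material loss has been shown.

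**What to change.** Add the register-size stratum as a fixed effect in the primary model and in the between-arm secondary models, or state that the full analysis plan already does so. Use the category in which each practice was actually randomised, not one recalculated later. The article's two categories leave a register of exactly 600 unassigned, so the analysis plan should record which side that value fell on at randomisation.

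The cost is one model term, already known for every randomised practice, and about one practice-level degree of freedom: about 0.4% in width from the t multiplier, and 0.5% in the simulation when the stratum is not prognostic. No new data are needed.

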### Primary and Secondary Outcomes

The primary outcome is the proportion (%) of eligible patients meeting both of the following CV risk factor targets: BP<130/80 mm Hg and TC<3.5 mmol/L. These outcomes were selected as they are current recommended care processes and clinical outcomes of care for the management of individuals with T2DM and MA [20,2].

Secondary outcomes include the following: incidence of CV events and all-cause mortality, smoking status glycemic control assessed by HbA_1c_, progression in MA assessed by change in ACR, kidney function measured by change in estimated *glomerular filtration rate* (e*GFR*), changes in T2DM, BP, and cholesterol-lowering medication prescribing, including contraindications and adverse reactions. Data extracted relate to blood samples that are previously collected as part of routine care and analyzed in accordance with relevant regulations and standard operating procedures.

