## Results

Baseline data have been extracted from 22 practices (12 controls and 10 interventions; Figure 1) with a reference date of October 30th, 2015. The total number of patients registered at participating practices is 232,639. There are 2721 patients with T2DM meeting the study MA criteria and eligible for the study. Of these 2721, 1067 patients (39.5%; 95% CI 37.7-41.4) had a code for MA or proteinuria in their electronic medical notes.

Biomedical characteristics, current risk factor control, medical history, and current drug prescriptions of the study population are shown in Tables 1-3. The mean age of patients is 62.9 (SD 10.0) years. There are no significant differences in number of male or female patients, and the study population, in keeping with local demographics, is predominantly of South Asian ethnicity (1136/1838 patients, 61.77%). The mean duration of T2DM is 10.5 (SD 7.2) years. Out of 2721 participants, 415 (15.25%) and 739 (27.16%) patients are current smokers and ex-smokers, respectively. Out of 2721 patients, 536 (19.70%) have chronic kidney disease stage 3.

The mean HbA_1c_ is 59.3 (SD 17.4) mmol/mol , mean systolic and diastolic BP (mm Hg) is 134.3 (SD 14.6) and 76.1 (SD 9.5) mm Hg, respectively, and mean TC is 4.1 (SD 0.98) mmol/L. Out of 2721 patients, 630 (23.15%) had achieved a tight BP target of <130/80 mm Hg and 707 patients (25.98%) had achieved a tight TC target of <3.5 mmol/L. Overall, 131 out of 2721 (4.81%) patients achieved all 3 “tight” CV risk factor targets. CV risk factor burden assessed by the prevalence of coronary heart disease, cerebrovascular disease, and peripheral vascular disease increased two-fold in those with eGFR<60 mL/min/1.73 m^2^ compared with those with eGFR≥60 mL/min/1.73 m^2^. Overall, 1076 out of 2721 (39.46%) individuals had a code for MA or proteinuria on their primary care medical record. Out of 2721 patients, 2064 (75.85%) were prescribed a nephroprotective agent, such as an angiotensin-converting enzyme inhibitor or an angiotensin receptor blocker drug, whereas 2070 patients (76.07%) were prescribed a cholesterol-lowering medication, that is, statin therapy.

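### On the natural reading, the primary model's individual-level baseline term is a yes/no flag; adding continuous baseline SBP, DBP and TC would be a cheap, modest gain in precision

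*Protocol article*

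**What the plan says.** The Analysis Plan section gives one rule for all outcomes, continuous and binary. The models are multilevel, linear or logistic as the outcome requires, and carry a random effect for practice. On covariates, the section says that they are "adjusted for the baseline value of the outcome both at practice and individual levels". Gaps in the baseline values are to be filled by an indicator approach, put there as "using the missing indicator method for “missing” baseline data".

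The Primary and Secondary Outcomes section makes the primary outcome binary: "The primary outcome is the proportion (%) of eligible patients meeting both of the following CV risk factor targets: BP<130/80 mm Hg and TC<3.5 mmol/L".

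The Results section and Table 1 show that the components are held at baseline as continuous measurements: "mean systolic and diastolic BP (mm Hg) is 134.3 (SD 14.6) and 76.1 (SD 9.5) mm Hg". TC is reported in the same way, with a mean of 4.1 and an SD of 0.98 mmol/L.

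The article does not state the functional form of the baseline covariate. It neither names nor excludes continuous SBP, DBP or TC as covariates in the primary model.

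**The concern.** If the baseline value of a yes/no outcome is itself yes/no, the individual-level term cannot tell a patient at 131/78 mm Hg with TC 3.6 mmol/L from one at 175/98 with TC 6.5. Both are coded as not meeting the targets, yet their chances of meeting them at 24 months plainly differ. The measurements that generate the flag are already extracted and carry that information.

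What is at stake is precision alone. The comparison rests on 22 practices (12 control, 10 intervention), a number that is now fixed, so the choice of covariates is one of the few remaining ways to narrow the interval.

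**Working it through.** **1. How little the flag distinguishes.** The article does not report how many patients met both targets at baseline. Table 1 gives BP<130/80 in 640/2721 = 23.5% and TC<3.5 in 707/2721 = 26.0%.
- If the two were independent (an assumption), 0.2352 × 0.2598 = 6.1% met both. The Results text gives 630 rather than 640 for BP, which makes this 6.0%.
- Lower bound: the 131 patients (4.81%) who met all three tight targets necessarily met these two.
- The Sample Size Considerations section assumes 7.5%.

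At 6.1% or 7.5%, 92.5 to 93.9% of patients share the value no.

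**2. Availability.** The Table 1 count of controlled risk factors classifies 673 + 1259 + 645 + 131 = 2708 of 2721 patients. Missingness therefore looks small, although unrecorded values might have been counted as not met.

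**3. What individual-level covariates can reach.** Planning inputs (Sample Size Considerations): 7.5% v 18%, ICC 0.05, mean 118 patients per practice, coefficient of variation (CV) of cluster size 1.11, 80% power, 5% significance (two-sided assumed).
- Individually randomised size: 154.5 per arm (unpooled variance) or 158 (pooled).
- Equal clusters: design effect 1 + 117 × 0.05 = 6.85. Practices per arm 154.5 × 6.85/118 = 8.97, or 158 × 6.85/118 = 9.17. The stated 9 per arm matches the first.
- CV 1.11: design effect 1 + ((1.11² + 1) × 118 − 1) × 0.05 = 14.12, which gives 18.5 to 18.9 per arm. The stated 9 is not reproduced with this inflation. That is a separate matter; here I use both design effects.
- Individual-level share of the variance, (1 − ICC)/design effect: 0.95/6.85 = 13.9%, or 0.95/14.12 = 6.7%.
- If the covariates add individual-level R² of 0.05 to 0.20 and explain nothing between practices, the SE falls by 1 − √(1 − share × R²): 0.3 to 1.4% (equal clusters) or 0.2 to 0.7% (CV 1.11).

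This is a floor. Patient mix differs between practices, so individual values also explain some between-practice variance.

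**4. Simulation A: continuous values added to the flag.** 22 practices (12 v 10), mean size about 118, size CV about 1, Table 1 means and SDs, composite ICC 0.048, 1500 trials per scenario, two-stage practice-level analysis that keeps the practice baseline. Assumed correlations: 0.3 to 0.45 within patients, 0.5 to 0.7 between practices.

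| SE, planned → with continuous | Change | Power |
|---|---|---|
| 0.0313 → 0.0298 | −4.8% | 0.723 → 0.742 |
| 0.0350 → 0.0339 | −3.1% | 0.643 → 0.651 |
| 0.0317 → 0.0302 | −4.7% | 0.717 → 0.751 |
| 0.0337 → 0.0320 | −5.0% | 0.926 → 0.943 |

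The false-positive rate was 0.060 for both models.

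**5. Simulation B: flag replaced by continuous values.** Random-intercept logistic model, 9 + 9 practices, size CV 1.11 clipped to 27–549, outcome ICC about 0.05, 7.5% v 18%, practice baseline proportion kept, 500 runs per scenario. Relative efficiency is the squared ratio of mean Z.

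| Patient / practice correlation | Relative efficiency | Equivalent SE cut, 1 − 1/√RE | Power (t, 16 df) |
|---|---|---|---|
| 0.3 / 0.5 | 1.056 | 2.7% | 80.2 → 81.4% |
| 0.5 / 0.5 | 1.062 | 3.0% | 80.8 → 82.8% |
| 0.7 / 0.5 | 1.018 | 0.9% | 81.6 → 82.6% |
| 0.5 / 0.8 | 1.195 | 8.5% | 89.6 → 94.0% |

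The Monte Carlo SE of each power figure is about 1.8 points before pairing. The false-positive rate was 8.0 to 9.6% in these two models, so the power figures are comparative only.

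- **Scale.** Raw log-odds SEs went 0.364 → 0.361, 0.371 → 0.380, 0.385 → 0.425 and 0.312 → 0.300. Two rose because the conditional coefficient grew as well (for example 1.234 → 1.379).
- **Practice term.** With no baseline adjustment, efficiency was 0.57 to 0.84 of the planned model.
- **Practice means of all three.** Adding these lowered efficiency, measured by the actual spread of estimates, to 0.83–0.94 of the flag model, while the model's own SEs shrank. That apparent gain is illusory.

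**6. Third check.** A marginal logistic model (GEE) with a practice-level baseline term gave a reduction in SE of about none to 4%.

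**The case against.** The strongest reply is that nothing here is wrong. A multilevel model with practice as random effect and baseline adjustment at both levels is valid and standard, and neither simulation points to bias. The functional form of a covariate is often left to the statistical analysis plan, which is not shown. Between-practice variance dominates, and the practice-level term already deals with it. The size of the gain rests on assumed correlations. Extra covariates also have costs: each needs handling of missing values, and in a logistic model they change the conditional odds ratio being estimated.

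Most of this stands. It rules out two stronger readings that a reader might be tempted to make:

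- **That the model adjusts only for a yes/no flag and gives away precision for nothing.** The practice-level baseline is adjusted for too, the yes/no form is an inference, and the alternative has small costs.
- **That a 3 to 5% cut in the standard error can be relied on.** Simulation A uses a two-stage practice-level analysis and not the planned multilevel logistic model. Simulation B and the marginal model give as little as 1% or nothing.

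Nor does the article document how unequal the 22 enrolled practices are; the 27–549 range and the CV of 1.11 are planning inputs.

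The reply does not remove the point. The article does fix the covariate as the baseline value of the outcome, and for the primary outcome the natural reading is coarse while better data are in hand. Both simulations kept a practice-level baseline term, so the gain is over and above it, and all eight scenarios favour the continuous values, although single power differences are close to Monte Carlo error.

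**Conclusion.** The point holds as an optional efficiency improvement. On the natural reading, the individual-level term in the primary model is a flag that very few patients carry at baseline, and it discards information in continuous SBP, DBP and TC that the trial already holds.

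The expected gain is about 0 to 5% off the standard error and roughly 0 to 4 points of power. The one scenario with very stable practice levels (correlation 0.8) did better, equivalent to 8.5% off the standard error and 4.4 points of power; I would not plan on that. Everything depends on baseline-to-24-month correlations, within patients and between practices, that the article does not report.

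The documents do not support calling the planned adjustment an error or a threat to validity, and the gain would not make up for a shortfall in the number of practices.

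**What to change.** Before the 24-month data are analysed, state in the analysis plan that the primary model:

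- includes baseline SBP, DBP and TC as continuous individual-level covariates, in addition to the baseline composite, with their functional form fixed in advance;
- keeps a single practice-level baseline term, and does not add practice means of all three measurements;
- handles missing baseline values by a stated rule for each covariate (under the planned missing-indicator method, one indicator each where needed);
- reports a standardised risk difference with a 95% CI beside the conditional odds ratio, because the added covariates slightly change what the odds ratio means.

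The cost is a few lines of analysis wording and three individual-level terms in a model with about 2700 patients. No new data are needed.

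### Baseline tests between arms, and the one baseline confidence interval printed, treat patients as independent although 22 practices were randomised

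*Protocol article*

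**What the plan says.** The Analysis Plan of the protocol article recognises clustering: "there is a high likelihood that biomedical characteristics may correlate within a cluster". For the trial outcomes it acts on this: "We will perform linear and logistic multilevel regression analyses to study the effects of the intervention with cluster as the random effect".

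For the baseline data the same section changes method. For proportions, "we will use Pearson chi-square to analyze differences in proportions between intervention and control groups". For continuous variables, independent-samples t "tests will be used to analyze differences in continuous variables between study groups". Neither sentence mentions practice.

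The Results section reports 2721 patients from 22 practices (12 control, 10 intervention). It gives one baseline interval, for coding of microalbuminuria or proteinuria: "1067 patients (39.5%; 95% CI 37.7-41.4". The Abstract, Table 1 and a later sentence of the same Results section give the count as 1076. Tables 1 and 3 print P values by arm.

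Sample Size Considerations states an ICC of .05 for meeting the blood pressure and cholesterol targets and a mean of 118 patients per practice. It adds: "The inflation for unequal cluster size is based on a coefficient of variation of 1.11".

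**The concern.** Practices were randomised, so the uncertainty in a between-arm comparison, or in a proportion pooled over practices, depends on variation between practices as well as on the number of patients. A patient-level chi-square or t test leaves the between-practice part out. Its P values are then too small and its intervals too narrow whenever the within-practice correlation is positive, which the article itself expects.

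Two things are at stake. The article presents its baseline estimates as a contribution in their own right, and the Discussion puts poor coding of microalbuminuria among its main baseline observations. The single interval attached to that figure overstates its precision. Also, 11 of the 53 P values in Tables 1 and 3 are below .05, against 2 to 3 expected (53 x .05 = 2.65) under randomisation with independent patients. The variables overlap, so this is only supportive, but it is the pattern that ignored clustering produces.

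**Working it through.** **1. Reproduce the printed interval.** p = 1076/2721 = .3954; SE = sqrt(.3954 x .6046/2721) = .00937; .3954 ± 1.96 x .00937 gives 37.7-41.4%, as printed. Wilson and exact intervals agree to the decimal shown. There is no cluster term. The count printed beside the interval, 1067, would give 39.2% (37.4-41.0%), so the interval belongs to 1076.

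**2. Reproduce printed P values.** Uncorrected Pearson chi-square on patient counts:
- Peripheral vascular disease, 48/1299 v 34/1422: chi-square 3.95, P = .047 (printed .047).
- Statin, 959/1299 v 1111/1422: 6.91, P = .009 (printed .01).
- GLP-1 agent, 56/1299 v 39/1422: 4.96, P = .026 (printed .03).
- Coding, 410/1299 v 666/1422: 66.24 (printed <.001).

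The plan was therefore applied as written for these variables.

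**3. Design effect.** DE = 1 + [(CV² + 1) x m - 1] x ICC, where m = 2721/22 = 123.7 patients per practice and CV is the coefficient of variation of practice size. CV is set to 0 (equal sizes) or to the planning value 1.11; realised practice sizes are not shown. The ICC of .05 is stated for the primary outcome only, so using it for baseline variables is an assumption. An ICC of .01 is a second assumption, to show the range.

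- ICC .05, CV 0: 1 + 122.7 x .05 = 7.1
- ICC .05, CV 1.11: 1 + (2.2321 x 123.7 - 1) x .05 = 14.8
- ICC .01, CV 0: 1 + 122.7 x .01 = 2.2
- ICC .01, CV 1.11: 1 + (2.2321 x 123.7 - 1) x .01 = 3.75

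**4. Consequences.** The SE is multiplied by sqrt(DE), the effective sample is 2721/DE, and the chi-square is divided by DE. The false-positive rate of a nominal 5% test is 2 x P(Z > 1.96/sqrt(DE)). Results use unrounded DE.

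| | ICC .01, CV 0 | ICC .01, CV 1.11 | ICC .05, CV 0 | ICC .05, CV 1.11 |
|---|---|---|---|---|
| DE | 2.2 | 3.75 | 7.1 | 14.8 |
| SE multiplier | 1.5 | 1.9 | 2.7 | 3.8 |
| Effective sample | 1222 | 725 | 381 | 184 |
| Coding CI, % | 36.8-42.3 | 36.0-43.1 | 34.6-44.5 | 32.5-46.6 |
| False-positive rate | 19% | 31% | 46% | 61% |
| Peripheral vascular disease P | .18 | .31 | .46 | .61 |
| Statin P | .08 | .18 | .33 | .49 |
| GLP-1 P | .14 | .25 | .41 | .56 |
| Coding difference P | <.001 | <.001 | .002 | .034 |

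**The case against.** The strongest reply is that nothing inferential depends on these tests. The outcome models carry a practice random effect, the sample size section includes an ICC, and the patient-level tests serve only to present baseline data. That stands, and it limits the point to reporting.

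A second reply is that the size of the error rests on a borrowed ICC. That also stands: the article gives no ICC for drug prescribing, vascular history or coding, and the CV is a planning value. The answer is to show a range. Even at an ICC of .01 the standard errors are 1.5 to 1.9 times the naive ones.

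A reader might infer more than the article supports:
- **That most of the small P values would vanish.** This depends on the ICC. Of the 11 below .05, seven remain so at ICC .01 with equal sizes: coding, ethnicity, revascularization, thiazolidinediones, transient ischemic attack, meglitinide and diastolic pressure. Three remain at ICC .05 with equal sizes: coding, ethnicity and thiazolidinediones (the last only just, at .042). The coding difference (31.56% v 46.84%) stays below .05 at every setting in the table.
- **That prevalence intervals are wrong.** None is printed; the only baseline interval is the one for coding.
- **That covariates will be chosen from these P values.** The Analysis Plan names the adjustment as the baseline value of the outcome at practice and individual level, and it selects nothing by baseline test.
- **That the article takes the tables to show failed randomisation.** It draws no such conclusion.

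**Conclusion.** The point holds as a fault of baseline reporting. The article expects within-practice correlation, models it for outcomes, and ignores it for the baseline tests and for the one baseline interval; the printed figures reproduce without any cluster term. Under assumed ICCs of .01 to .05, with equal or planned unequal practice sizes, the coding interval should be about 1.5 to 3.8 times as wide as printed. A nominal 5% baseline test would reject falsely about 19% to 61% of the time. The P values for peripheral vascular disease, statin and GLP-1 exceed .05 across that range, while the coding difference does not.

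That the patient-level method was used is certain. How much it matters is conditional on ICCs that the article does not give and that the patient data could supply. The planned estimate of the intervention effect is not affected.

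**What to change.** Drop the P values from Tables 1 and 3 and describe balance by arm with patient-level summaries and practice-level summaries (for example, the spread of practice means or proportions). If between-arm baseline tests are kept, take them from the same practice random-effect model that is planned for the outcomes and amend the Analysis Plan sentence to match. Replace the coding interval with a cluster-robust or practice-level one, and settle whether the count is 1067 or 1076 when doing so.

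The cost is re-running the baseline tables on data already extracted, and accepting a wider interval. The design, sample size and outcome analysis are unchanged.
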